**Aim 1:** To test the effect of the Sprouts intervention on the following changes in health outcomes for the child: a) FV intake; b) dietary psychosocial variables; c) anthropometric parameters (e.g., BMI, WC, percent body fat); d) metabolic risk factors (e.g., blood pressure, metabolic syndrome, fasting glucose, insulin, and lipids); and e) home environment (e.g., availability and accessibility of FV).

***Hypothesis 1:*** Sprouts intervention students compared to control students will have, as primary outcomes: increased vegetable intake and reduced BMI z-scores, WC, fasting glucose, and insulin; and, as secondary outcomes: increased fruit and fiber intake and reduced added sugar intake, improved dietary psychosocial variables (i.e., preference and motivation, self-efficacy for FV), and reduced body fat and other metabolic risk factors.

**Aim 2:** To test the effects of the TX Sprouts intervention on changes in dietary intake and related dietary psychosocial variables of the parents.

**Hypothesis 2:** TX Sprouts intervention parents compared to control parents will have increased FV intake, improved psychosocial variables linked to FV intake, and improved access and availability of FV in the home.

**Exploratory Aim:** To identify specific strategies/components of the TX Sprouts intervention that were implemented and sustained at the completion of the intervention, which will provide valuable information on how to disseminate and sustain long-term garden programs in schools.

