## 5. Measures

**Anthropometrics, Body Fat, and Blood Pressure:** For both children and parents, weight will be measured using a SECA (model 869) digital scale to the nearest 0.1 kg, and height will be measured using a wall-mounted stadiometer to the nearest 0.1 cm. BMI ( $\text{kg/m}^2$ ) and BMI percentiles for CDC age- and gender-specific values will be determined using EpiInfo 2005, (CDC, Atlanta, GA). Waist circumferences (WC) will be measured and recorded to the nearest 0.1 cm. Body composition will be assessed using Bioelectrical Impedance with the Tanita Body Fat Analyzer (model TBF 300). Blood pressure will be obtained in duplicate with an automatic cuff according to recommendations of the American Heart Association. A skin carotenoid scan will be completed of the finger, which will take approximately 20 seconds. This is a noninvasive device that measures carotenoids in the skin to assess fruit and vegetable consumption. The device uses a technique called reflectance spectroscopy, which involves shining a light on the skin of one finger to measure carotenoids in the skin which gives us an objective measures of vegetable intake.

Parental height, weight, body fat, WC, and blood pressure will be collected at first and last family workshop (expecting a subsample only). Therefore we will ask self-reported height and weight in questionnaire packets.

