| 0.05                                                                                          | power       | 0.8                                                                                                                 | 12              | 6                | 4                   | 12               | 14                                                | 12              |
|                                                                                               |             | 0.9                                                                                                                 | 16              | 8                | 6                   | 16               | 20                                                | 16              |
| 0.01                                                                                          | effect      | 0.8                                                                                                                 | 18              | 8                | 6                   | 18               | 24                                                | 18              |
|                                                                                               |             | 0.9                                                                                                                 | 22              | 10               | 8                   | 22               | 30                                                | 24              |
| ICC: intraclass correlation coefficient; $\sigma^2$ : variance within schools from pilot data |             |                                                                                                                     |                 |                  |                     |                  |                                                   |                 |

ICC: intraclass correlation coefficient;  $\sigma^2$ : variance within schools from pilot data

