measurements from baseline to end of study. We assumed that a cluster average size of 127 children per school would have pre and post measurements for vegetable intake, BMI z-scores, and waist circumference but only 60 children per school for blood glucose and insulin values. **Table 2** presents the minimum number of schools needed for power of 80% and 90% for the children's primary outcomes using a type I error of 0.05 and 0.01, a two-sided test, and assuming equal allocation between the two arms. The variance ( $\sigma^2$ ) within schools and the intraclass correlation coefficient (ICC) to estimate the sample size were obtained from the R21 pilot study. Therefore, with six schools and 60 children per school with blood draws, 360 children are needed, and given our preliminary data and attrition rates, we will have enough power to detect the effect size of a decrease in 2.13 mg/dL in fasting glucose. For the children, we will also have enough power to detect an effect size above 0.5 in vegetable (serv/d) intake, a decrease of 0.065 in BMI z-scores, a decrease of at least 0.02 cm in waist circumference, and a decrease of at least 12  $\mu$ U/ml in fasting insulin. **For Aim 2**, we estimate the power of this study for the parents using vegetable intake and availability from Castro et al using the same powers and type I error levels as we used for the

children as well as the R21 pilot data for the variance and ICC. Among the parents, we will have enough power to detect an effect size above 0.5 vegetable intake (serv/d) (**Table 2**).

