#### **e. Recruitment**

A flow chart depicting the study participants through the study appears in **Figure 1**. Sixteen elementary schools will be allocated to either TX Sprouts intervention (n=8 schools) or Control group (n=8 schools). The schools from the sampling frame average approximately 300 3rd-5th grade students for a total of 4,800 3rd-5th grade students. All participants and their parents will have to sign assent and consent forms, approved by UT-Austin's Institutional Review Board. Based on previous intervention work with Hispanic communities, we anticipate ~50% of parents will consent for their children to participate, and their children will complete all the baseline measures (n=2,400). We anticipate 15% attrition at post-intervention measurement due to parents/students moving away or being sick or absent from school, which would mean that 2,040 children (or 127 children per school) would complete the post-testing measures in one school year. Based on blood draw participation rates in LA Sprouts, we anticipate that 50% of participating children (n=1,200) will also participate in the blood draws at pre-intervention and 40% (n=960 or 60 per school) at post-intervention.

Important components of our recruitment and retention strategy developed from numerous years of research with Hispanic children/families include: 1) bilingual staff, 2) Spanish and English forms/questionnaires written at a 3rd grade reading level, and 3) incentives for participation.

We will attempt to recruit approximately 10-15 school stakeholders (i.e., teachers, principals, administration staff) and 5-10 GLCs members to conduct structured interviews with over sustainability issue. The principals at each school will likely help recruit these individuals.

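### The 0.02 cm waist circumference effect and its Table 2 variance of 0.005 cannot credibly both be in centimetres, so the unit or the inputs need correcting

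*Protocol*

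**What the plan says.** Hypothesis 1 in section 3 lists, "as primary outcomes: increased vegetable intake and reduced BMI z-scores, WC, fasting glucose, and insulin". In section 5, the Sample Size and Power Analysis rests on the change from baseline to end of study. For waist circumference, Table 2 gives an ICC of 0.019, a variance of 0.005 and an effect of -0.020, and requires 12 and 16 schools for 80% and 90% power at alpha 0.05 (18 and 22 at alpha 0.01). The table footnote describes the variance as "variance within schools from pilot data". The table prints no unit for the waist effect or variance. The unit comes from the text, which promises enough power for "a decrease of at least 0.02 cm in waist circumference".

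The anthropometrics paragraph of the same section says: "Waist circumferences (WC) will be measured and recorded to the nearest 0.1 cm".

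**The concern.** If the unit in the text applies to the table, the variance is 0.005 cm², so children's waist change over a school year would have an SD of about 0.07 cm. That is smaller than the step to which each reading is recorded. It would have to cover growth, tape placement, true differences between children and rounding in 8- to 11-year-olds.

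At stake is the power statement for a primary outcome. A reader cannot tell whether the trial is powered for 0.02 cm, for 2 cm, or for a quantity other than waist circumference. A null waist result could then be misread as ruling out very small effects.

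**Working it through.** **Inputs.** From Table 2: effect d = 0.020, variance s² = 0.005, ICC = 0.019. From the power text: m = 127 children per school ("We assumed that a cluster average size of 127 children per school would have pre and post measurements"), "using a type I error of 0.05 and 0.01, a two-sided test, and assuming equal allocation between the two arms", and "power of 80% and 90% for the children's primary outcomes". The 127 already allows for dropout ("We anticipate 15% attrition at post-intervention measurement"): 2,400 × 0.85 / 16 = 127.5. The trial has 8 schools per arm. The recording step is h = 0.1 cm.

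**1. Reproducing the plan's figure.**
Schools per arm = 2 s² (z_α/2 + z_power)² / d² × [1 + (m − 1) ICC] / m. The design effect is 1 + 126 × 0.019 = 3.394.

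| Alpha | Power | Schools per arm | Total, rounded up | Table 2 |
|---|---|---|---|---|
| 0.05 | 80% | 5.24 | 12 | 12 |
| 0.05 | 90% | 7.02 | 16 | 16 |
| 0.01 | 80% | 7.80 | 16 | 18 |
| 0.01 | 90% | 9.94 | 20 | 22 |

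The alpha 0.05 counts match exactly. Any unrounded variance from 0.00513 to 0.00549, which would print as 0.005, gives all four cells. The counts were therefore very probably computed from these inputs.

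**2. What the inputs mean in centimetres.**
- SD of change = √0.005 = 0.0707 cm, against a recording step of 0.1 cm.
- Variance from rounding two readings = 2 × h²/12 = 2 × 0.01/12 = 0.00167 cm², and 0.00167/0.005 = one third.
- What remains for everything else is 0.005 − 0.00167 = 0.00333 cm², an SD of 0.058 cm.

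**3. Does rounding by itself remove the power?** No.
- SE of the difference with 8 schools per arm = √[2 × 0.005 × 3.394 / (127 × 8)] = 0.00578, and 0.02/0.00578 = 3.46. Power is 0.93 by the normal approximation and 0.90 by t on 14 df.
- In a simulation of 4,000 trials with variance 0.005, both readings rounded to 0.1 cm and a t test on school means, power for 0.02 cm was about 0.87. The rejection rate under the null was 0.048.

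**4. Metres (an assumption; the protocol does not say so).**
- Effect 0.02 m = 2 cm, variance 0.005 × 10,000 = 50 cm², SD 7.07 cm.
- Power depends only on d²/s², so the school counts and the power (0.90, t on 14 df) do not change.
- Difference detectable with 80% power = (2.145 + 0.868) × SE = 3.013 × 0.578 = 1.74 cm.

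**5. Illustration with assumed change SDs in centimetres (not in the protocol).** Same ICC, cluster size and 16 schools; t on 14 df for the detectable difference, normal approximation for the power.

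| Assumed SD (cm) | SE (cm) | Detectable with 80% power (cm) | Power for a true 0.02 cm |
|---|---|---|---|
| 0.5 | 0.041 | 0.12 | 8% |
| 2 | 0.163 | 0.49 | 5% |
| 3 | 0.245 | 0.74 | 5% |
| 5 | 0.409 | 1.23 | 5% |

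**The case against.** The best defence is that the calculation is internally sound. The alpha 0.05 counts reproduce exactly, and a unit error common to both inputs cancels. If metres were used, one label is wrong and the design is untouched. All of this stands.

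A reader might also infer that an effect of one fifth of the recording step cannot be detected, so that the claimed power does not exist. The documents do not support this. The quantity tested is a difference in mean change between arms of about 1,000 children each (8 × 127 = 1,016), and such a difference can be smaller than the step of a single reading. On the printed inputs, rounding lowers power only from 0.90 to about 0.87.

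Nor do the documents support a fixed multiple of error. Dividing 0.49 to 1.74 cm by 0.02 cm gives roughly 25 to 87, but the lower end rests on an SD that the protocol does not give. The upper end compares a result in metres with a label in centimetres; like for like it is 1.74 cm against 2 cm.

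The defence does not rescue the sentence as printed. An SD of change of 0.07 cm is not credible for tape-measured waist circumference in growing children, whatever the table's internal consistency.

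**Conclusion.** The point holds in this form: the waist effect and variance cannot credibly both be in centimetres, so the stated detectable effect of 0.02 cm on a primary outcome cannot be relied on. The defect is the unit or identity of the inputs. An absence of power is not shown.

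The consequence depends on what the pilot variable was. If both inputs were in metres, the effect is 2 cm and 16 schools give about 90% power. If the variable was a ratio, or a value was mistranscribed, the power for waist circumference is unknown. If the effect really is 0.02 cm and the SD of change is 2 cm or more (assumed), power is about 5%. Metres is a natural guess, but it remains a guess without the pilot data. For the same reason the documents cannot settle whether 16 schools are enough for this outcome.

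**What to change.** Go back to the pilot data, state the unit and the SD of change in waist circumference, and correct both the power sentence and the Table 2 column.

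- **If both inputs were in metres:** restate the effect as 2 cm with variance about 50 cm². The school counts stand. Add that 16 schools give about 90% power for 2 cm and can detect about 1.7 cm with 80% power.
- **If the variable was a ratio, or a value was mistranscribed:** relabel the column, recompute it for waist circumference in centimetres, and restate the detectable difference for 16 schools.

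The edit is one table column and one sentence. The price is that the stated detectable effect becomes less favourable than 0.02 cm.

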### **TX Sprouts Research Evaluation:**

Evaluation measures will be collected at baseline and end of the school year in both treatments (intervention and control schools). Measurements will occur during the first four weeks of school in the fall and the last four weeks of school in the spring. Most measures on children will be collected at the schools during normal school hours. The fasting blood draws will occur first thing in the morning before school starts. The following evaluation measures will be obtained from students at baseline and post-intervention:

- Measured height, weight, BMI parameters, waist circumference (WC), body composition (via bioimpedance); carotenoid scan of skin
- Blood pressure via child-specific automated cuff;
- Subsample of students will complete three 24-hour diet recalls by telephone;
- Child survey assessing dietary intake via food screener and related determinants of dietary behaviors (e.g., preference/motivation/self-efficacy to eat FV);
- Program lessons may also be audio/visual recorded;
- Voluntary fasting blood sample to assess glucose, insulin, and lipid parameters;
- Accelerometers to measure physical activity;
- Time on Task observations

Parent questionnaires will be handed out or mailed to the homes after consent is obtained at baseline and post-intervention. Questionnaires are translated into Spanish, culturally appropriate, and take ~60 minutes to complete. We will encourage parents to complete the questionnaire before the first family lesson and return it via mail (pre-paid postage will be provided). However, parents will also be able to complete the questionnaire at the first and last lessons. Parent surveys will evaluate the following: food security via USDA validated questions, confidence cooking, dietary intake via validated screener, reported height and weight, medical history, basic demographics, child feeding practices and food home environment from CEBQ and TGEQ, and preferences adapted from Domel et al. We will also attempt to measure height and weight on a subsample of parents, which will occur at the first and last parent lesson. Parent workshops may also be audio/visually recorded.

After the intervention year, we will conduct a series of structured interviews (30 minutes or less per interview) as well as surveys, with participating school stakeholders (i.e., principals, teachers,

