**Data Collection:** Some study data will be collected and/or managed using REDCap (Research Electronic Data Capture). REDCap is a secure, web application designed to support data capture for research studies, providing user-friendly web-based case report forms, real-time data entry validation (e.g. for data types and range checks), audit trails and a de-identified data export mechanism to common statistical packages (SPSS, SAS, Stata, R/S-Plus). REDCap also provides a powerful tool for building and managing online surveys. The research team can create and design surveys in a web browser and engage potential respondents using a variety of notification methods. The system was developed by a multi-institutional consortium, which includes University of Texas at Austin and was initiated at Vanderbilt University. The database is hosted at the Population Research Center, which will be used as a central location for data processing and management. The PRC server has been cleared for Category-I data collection by UT's Information Security Office. Network transmissions (data entry, survey submission, web browsing, etc.) in REDCap are protected via Secure Sockets Layer (SSL) encryption. REDCap data collection projects rely on a thorough study-specific data dictionary defined in an iterative self-documenting process by all members of the research team with planning assistance from the PRC. The iterative development and testing process results in a well-planned data collection strategy for individual studies. REDCap provides a secure, web-based application that is flexible enough to be used for a variety of types of research, provide an intuitive interface for users to enter data and have real time validation rules at the time of entry.

**Sample Size and Power Analysis: For Aim 1:** We estimated the power of this study for children using pilot data from five primary variables from LA Sprouts: vegetable intake (serv/d), BMI z-scores, waist circumference, fasting glucose (mg/dL) and fasting insulin ( $\mu$ U/ml). We estimated minimum sample size using several effect sizes on the difference between intervention and control group on the change of

**Table 2:** Minimum number of schools required evaluating the differences in the effect sizes between

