**Data Analyses:** Summary statistics, graphical analyses, and frequency distributions will be used to describe the data between the intervention and control groups. Data will be transformed if needed. We will handle missing data using two primary approaches: multiple imputation and full information maximum likelihood estimation methods. Each method has potential biases and makes assumptions about the underlying basis for the missing data (e.g., missing at random-MAR) and other features of the data that are present. However, we have included enough baseline variables of the participants and at the follow-up visits to make the MAR assumption plausible. Without prior knowledge of the missing data process, we will have to explore the implications of applying different strategies. **For Aim 1:** We will test if the children and parents participating in Sprouts compared to control will have increased changes in average consumption of vegetable servings per day and decreased average changes in BMI z-scores, waist circumference, fasting glucose, and insulin using well-known statistical methods for cluster randomized trials. Several analytic strategies will be employed to determine the effect of the intervention on vegetable intake and many of the other primary outcome variables. We plan to conduct a two-stage nested analysis of variance model, which is a special case of the mixed effects linear regression model also known as a repeated measures analysis of variance model. The terms in the model include the true mean for the outcome variable, the fixed effects of the intervention arm, one random cluster effect (school), and the random error term. In this case, the schools (clusters) should be regarded as nested within the intervention arms and the students or parents within the school (clusters). We will model the pattern of covariance among observations as an unstructured variance–covariance matrix because of the small number of repeated assessments. We will also explore interaction effects between intervention group and selected covariates to determine whether the intervention was more effective for some covariates. For example, we will test whether the effectiveness of the intervention varied by age, gender, race/ethnicity, baseline BMI, percent free and reduced lunches, physical activity measures, class attendance, and wave of data collection. These tests will be considered as exploratory analysis and treated as hypothesis generating and interpreted with caution. The analytic approach for the secondary outcome measures (i.e., blood pressure, percent body fat, metabolic syndrome, adipocytokines, other dietary intake variables, and related dietary psychosocial behaviors) will involve a similar use of linear mixed models. Again, school will be modeled as a random effect nested within treatment arm, and treatment arm will be modeled as fixed effects. **For Aim 2:** To test the effects of the Sprouts intervention on changes in vegetable intake and availability and on related dietary behaviors in the parents, we will use similar and well-known statistical methods as described for Aim 1. As exploratory and secondary analyses, we intend to conduct structural equation modeling (SEM) with established mediational (and direct) effects, with and without the cluster effect variables, to examine how changes in behaviors, as well as program fidelity (attendance, dosage, delivery of intervention) impacts changes in main health outcomes. For the **Exploratory Aim**, we will conduct descriptive statistics on the collected pilot data of the sustainability strategies (qualitative and quantitative data obtained via structured interviews and focus groups) on both intervention and control schools. The unit of analysis will change, as these measurements will be collected on teachers, principals, GLCs, administration staff, district directors and staff. We will obtain pilot data on the differences between intervention and control schools on the following: number of curriculum lessons taught, use and maintenance of garden, successful components/strategies implemented to sustain program, and additional material/resources/training requested, etc. This pilot data will serve to consider future projects to sustain the program and for power and sample size purposes.

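### The Aim 1 primary analysis mixes two incompatible models, and fitted as labelled its arm effect is not the effect on change

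*Protocol*

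**What the plan says.** Protocol section 5, Data Analyses, For Aim 1, plans a two-stage nested analysis of variance and describes it as a "special case of the mixed effects linear regression model also known as a repeated measures analysis of variance model". It then gives the contents: "The terms in the model include the true mean for the outcome variable, the fixed effects of the intervention arm, one random cluster effect" for school, and a random error. The covariance among observations is to be an "unstructured variance–covariance matrix because of the small number of repeated assessments". No time, arm-by-time, school-by-time or baseline term is listed. Baseline BMI appears only in the exploratory work on effect modification, where "we will test whether the effectiveness of the intervention varied by age, gender, race/ethnicity, baseline BMI" and further covariates.

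The target is stated in the same paragraph: Sprouts participants "will have increased changes in average consumption of vegetable servings per day and decreased average changes in BMI z-scores", and likewise for the other primary outcomes. The sample-size text works from "effect sizes on the difference between intervention and control group on the change of" the measurements between baseline and study end. There are two occasions (section 4, TX Sprouts Research Evaluation): "Evaluation measures will be collected at baseline and end of the school year in both treatments".

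The secondary outcomes and Aim 2 are to be analysed in a similar way. The text on secondary outcomes again has school as random and arm as fixed, with nothing for time.

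**The concern.** A model that is repeated-measures by label and by covariance takes two rows per child. With two rows per child and no time or arm-by-time term, the arm coefficient is a difference between arms averaged over both occasions. Randomisation makes the expected baseline difference zero, so this average is not the difference in change that the trial is meant to test and is powered for.

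The alternative is one change score per child. The listed terms then fit, but there are no repeated assessments left for the covariance sentence to describe.

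The paragraph governs all five child primary outcomes and, by reference, the secondary outcomes and Aim 2. Until it is resolved, two analysts could follow it faithfully and report different estimands. The choice could also be made after the data are seen.

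**Working it through.** **Inputs.** From the protocol: 16 schools, 8 per arm (section 6, Recruitment); 127 children per school for diet, BMI z-score and waist, and 60 for glucose and insulin; the Table 2 ICCs and variances; 15% attrition, with blood draws falling from 1,200 to 960, which is 20%. Assumed, because the protocol gives neither: the pre-post correlation ρ and the ratio of post to pre SD.

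**1. The plan's own figure.** Table 2 gives 6 schools for glucose at two-sided 0.05 and 80% power. The change-score formula for a cluster trial is

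k per arm = (1.96 + 0.8416)² × 2σ²[1 + (m − 1)ICC] / (mδ²).

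With σ² = 40.86, ICC = 0.001, m = 60 and δ = 2.133, this is 7.849 × 2 × 40.86 × 1.059 / (60 × 4.550) = 2.49. Rounded up, that is 3 per arm, or 6 schools, as stated. The BMI z-score column also reproduces in full (4, 6, 6, 8). Waist reproduces at 0.05 only. Vegetable intake reproduces only if 0.08 is read as a between-school variance. Insulin does not reproduce. Where Table 2 can be reproduced, it is powered on change.

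**2. Listed terms fitted to two records per child.** The expected arm coefficient is w × δ, where w is the weight that generalised least squares gives the post record. With R = SD post / SD pre and complete data,

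w = (1 − ρR) / (1 + R² − 2ρR).

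- R = 1: w = 0.50 for any ρ.
- R from 0.9 to 1.1 at ρ = 0.5: w from 0.60 to 0.41.
- R from 0.9 to 1.1 over ρ = 0.3 to 0.9: w from 1.00 to 0.04.

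With a fraction q missing at post only and R = 1, w = [(1 − q)/(1 + ρ)] / [2(1 − q)/(1 + ρ) + q].

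- q = 0.15: 0.43 to 0.45 for ρ from 0.9 to 0.3.
- q = 0.20: 0.40 to 0.43.

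**3. Check by simulation.** Sixty trials of 16 schools × 127 children were simulated with a true effect of 0.50 serv/d, ρ = 0.5 and a common time trend of 0.3. The fits used a random school intercept and independent residuals. Mean estimates, with Monte Carlo standard errors:

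| Model | Mean estimate |
|---|---|
| Listed terms, two rows per child | 0.247 (0.017) |
| Arm-by-time, two rows per child | 0.502 (0.007) |
| Listed terms, one change score per child | 0.502 (0.007) |

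**4. Illustration of lost power (glucose, 16 × 60, R = 1, complete data).** This takes the variance of change as 40.86 and applies the stated ICC to levels as well. Power for change is 0.999. The listed terms on two rows give 0.96, 0.83, 0.56 and 0.21 at ρ = 0.3, 0.5, 0.7 and 0.9.

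**5. What baseline adjustment adds to a change score.** At equal SDs the child-level variance ratio is (1 − ρ²) / [2(1 − ρ)] = (1 + ρ)/2, a reduction of 35%, 25% or 15% at ρ = 0.3, 0.5 or 0.7. Only the child-level share of a school mean's variance shrinks. That share is [(1 − ICC)/m] / [ICC + (1 − ICC)/m].

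| Outcome | Share | Total variance reduction (ρ = 0.3, 0.5, 0.7) |
|---|---|---|
| Vegetable intake (0.071, m = 127) | 0.093 | 3%, 2%, 1% |
| BMI z-score (0.002, m = 127) | 0.797 | 28%, 20%, 12% |
| Glucose (0.001, m = 60) | 0.943 | 33%, 24%, 14% |

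This assumes that baseline explains none of the between-school variation in change.

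**6. What a two-occasion repair must include.** If arm-by-time were added with only a school intercept, that intercept would cancel from change and clustering of change would go uncounted. Taking the Table 2 ICCs as ICCs of change, the rejection rate of a nominal 5% test under the null is 2[1 − Φ(1.96/√D)], with D = 1 + (m − 1)ICC.

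| Outcome | D | Rejection rate |
|---|---|---|
| Glucose | 1.059 | 6% |
| BMI z-score | 1.252 | 8% |
| Waist | 3.394 | 29% |
| Vegetable intake | 9.946 | 53% |
| Insulin | 33.69 | 74% |

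**The case against.** The best defence is that a change score is plainly meant. The hypothesis speaks of changes, the power calculation is on change, and mean, arm, random school and error is then a standard cluster-trial model. It is unbiased, it accounts for clustering of change, and it needs no time terms. All of that stands. A reader might infer that the primary analysis halves the treatment effect. The documents do not support that as a flat statement, because it holds on one of two readings only. Even there, one half is exact only with equal SDs and complete data.

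A reader might also infer a type I error near 53%. That figure belongs to a model with arm-by-time and a lone school intercept, which the plan never lists, and to vegetable intake alone. Step 6 is a warning for one possible repair and not a fault in the stated terms.

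Nor is an unadjusted change score an error. Baseline adjustment is a matter of efficiency, its gain for vegetable intake is about 2% at an assumed correlation of 0.5, and a separate analysis plan could settle it.

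The defence does not remove the contradiction. The paragraph never says that the modelled outcome is a change score. Its only description of the data structure is the reason given for the covariance, "because of the small number of repeated assessments". It also announces several analytic strategies without ranking them. This is not detail left for later: the text fixes a label, a list of terms and a covariance that do not fit together.

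**Conclusion.** The point holds as an internal contradiction in the primary analysis, and it should be corrected before any outcome is analysed. On the change-score reading the estimate is sound, and only the label and the covariance sentence are out of place. On the reading that the label and covariance invite, the arm effect does not estimate the stated target. It is about 0.50 of the true effect at equal SDs with complete data, and about 0.43 to 0.45 with 15% post-only missingness. It is sensitive to unequal SDs, and its exact size is unknown because the protocol gives neither the pre-post correlation nor the two SDs. The power figures in step 4 are illustrative for the same reason.

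**What to change.** Replace the sentences on model label, terms and covariance with one model.

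- **Preferred:** post-intervention value = arm + child's baseline value + random school + error, with arm tested on school-level degrees of freedom (16 − 2 = 14 with these terms). Adjustment uses a measurement that is already planned. The gain is small for vegetable intake and larger for low-ICC outcomes such as glucose and BMI z-score, depending on the correlation.
- **Also valid:** change score = arm + random school + error, with the repeated-measures label and the unstructured-covariance sentence removed.
- **If a two-occasion model is kept:** include time and arm-by-time, name arm-by-time as the effect, add a random school-by-time effect so that clustering of change is counted, and apply the unstructured covariance within child only.

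Use the same wording for Aim 2 and the secondary outcomes. The cost is a rewritten paragraph. Both measurements are already in the schedule, and the sample size need not change on this account, since the power calculation is framed on change.
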